## Discussion

Our study is a pragmatic clinical study involving a marginalized patient population that is often excluded from participating in clinical trials due to lower health literacy and marginalization [23].

A potential methodological limitation in this study is the possibility of measurement errors arising from the use of social nurses rather than nurses with specialized respiratory training to conduct spirometry. To mitigate these risks, training is provided through local respiratory medical staff. Additionally, the social nurses are also required to be familiar with the Danish standard for lung function testing [24]. Moreover, social nurses interact directly with five to eight patients during a day shift, based on a subjective assessment of which patients need the most attention. This results in a carefully selected group of marginalized patients, potentially introducing selection bias between the study sites.

Furthermore, the handheld technical equipment used for performing the lung function test may increase the risk of measurement errors. Hence, we cannot make a definite diagnosis of COPD, but detect a possible impairment or obstructive pattern in the spirometric values. When suspicion of lung disease arises, patients undergo the standard diagnostic procedure at the current hospital, with some patients assessed in the outpatient clinic and others referred to their general practitioner. Since we cannot retrieve diagnosis from general practitioners, diagnosis verification is only available for those who attend the outpatient clinic. The five-year follow-up will determine if patients receive regular prescribed medication, facilitating confirmation of the COPD diagnosis.

We employ post-BD spirometry utilizing airflow limitation as the criterion for COPD diagnosis. Although COPD is the predominant cause of irreversible airflow limitation, it is noteworthy that a minority of patients, including those with conditions such as bronchiectasis, cannot be entirely ruled out from our study cohort. Further, an essential consideration involves the exclusion of individuals with severe, acute illnesses from the assessment of COPD prevalence due to their inability to actively participate in lung function measurements.

A strength of the study is the use of a multi-centre design on a national level, which thus with a high degree of validity reflects this subgroup of the Danish population.

The socially marginalized group is often overlooked in research [15], and this study aims to contribute to our understanding of the long-term morbidity and mortality associated with smoking in this population. By doing so, we can enhance our knowledge of the detrimental health effects of tobacco within the context of challenging social circumstances. Additionally, the collection of patient-reported outcome measure (PROM) data through the CAT form will provide valuable insights into the daily symptom burden experienced by both smokers and non-smokers within this patient group. These unique data will offer an in-depth understanding of the respiratory-related everyday experiences of socially marginalized people in Denmark. Should the study demonstrate an increased symptom burden, morbidity, and mortality associated with tobacco smoking, it might warrant further investigation into more intensive smoking cessation treatment or harm reduction strategies involving nicotine substitution.

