## Material and methods

### Study setting

Study participants are identified during hospitalization at the participating hospitals, that is admission to emergency, medical and surgery departments, and recruited by social nurses, working at 11 hospitals within three of the five Danish regions (Capital Region of Denmark, Region Zealand, and Central Denmark Region). The hospitals include both urban and rural areas. Patient recruitment commenced on April 19th, 2021 and is still enrolling patients, with an anticipated completion of enrolment in 2024.

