### Data collection

#### Baseline

Baseline data are derived from lung function measurements and the interviews and questionnaires completed at inclusion.

The data is sampled online by social nurses using a smartphone or tablet, and the data is directly entered into REDCap (Research Electronic Data Capture) [19]. Further, the results of the spirometry are uploaded directly from the smartphone to REDCap.

If online data entry is not possible, a paper version of the survey will be available. At the end of the inclusion period, they will be sent to the Department of Clinical Research at Hvidovre Hospital and entered manually into REDCap.

Upon reaching the necessary number of participants, the local investigators will refer to the outpatient bookings and physician notes in the electronic patient record, to determine whether the participants underwent further evaluation at a department of respiratory medicine and if a diagnosis of COPD was confirmed (as indicated by ICD10 coding J44).

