#### Five-year follow-up

Follow-up at 5 years will be performed using the unique civil registration number (Central Person Register (CPR) number) [20] through linkage to national Danish registers. A CPR number is a unique personal identification number assigned to all residents in Denmark. The CPR number consists of a unique 10 digits and includes information about the person’s date of birth.

Data on healthcare utilisation and hospital contacts in the cohort will be obtained from the Danish National Patient Register (NPR), and mortality data will be obtained from the Cause of Death Register. Data on redeemed prescriptions for COPD medication will be obtained from The Danish National Database of Reimbursed Prescriptions.

Patients’ labour market attachment and income basis are based on extractions from the Register-based Labour Force Statistics (RAS), administered by Statistics Denmark. Data on the highest acquired level of education (HFAUDD) will be obtained from Statistics Denmark.

The CPR numbers and collected survey data from REDCap for the study participants are transferred to Statistics Denmark (DST), where they are combined with information from the Danish National Patient Register, the Cause of Death Register, and the Danish National Database of Reimbursed Prescriptions. Data processing at DST is conducted using pseudonymized data within a secure server environment.

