### Variables

#### Self-reported demographic variables

Demographic variables included sex and age at inclusion. The development of COPD is strongly associated with age and will be presented as a categorical variable in the following categories: 18–24, 25–34, 35–44, 45–54, 55–64, 65–79, 80+ years.

The categories for the highest completed education are divided into the following: incomplete primary school, primary school (completed 9th or 10th grade), high school/gymnasium, vocational education, tertiary education (short/2 years, medium/3–4 years, and long/5–6 years).

The indicator regarding attachment to the labour market is divided into three categories: employed, unemployed, and out of the workforce.

Housing conditions are included to describe the degree of vulnerability and include questions related to housing situation, type of housing/rough sleeping and whether they live alone or with others.

Symptom burden and impact on quality of life in patients diagnosed with COPD is evaluated using the COPD Assessment Test (CAT) [21], a validated questionnaire specifically designed to assess various aspects of their daily respiratory symptoms and limitations in daily activities.

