#### Clinical variables

The patients enrolled in this study may be categorized into four groups according to their diagnostic status: those previously diagnosed with COPD (self-reported), those identified as having COPD through screening, those without COPD as determined by screening, and those with an unknown diagnostic status due to insufficient lung function test. COPD identified through screening refers to people whose post-bronchodilator FEV1/FVC ratio is less than 0,7, according to the measurements obtained by the social nurse.

When assessing the prevalence of COPD, the groups diagnosed through screening and self-reported COPD are considered. Participants who are unable to perform spirometry are classified as having an unknown diagnostic status and are not included in the calculation of COPD prevalence.

At the 5-year follow-up, the prevalence of patients diagnosed with COPD after screening is identified either through the National Patient Health registry based on the ICD10 code J.44 or by examining prescriptions for COPD medication (including all types of inhalation medicine) recorded in The Danish National Prescription Database.

The utilization of healthcare services is evaluated based on all hospital contacts, including outpatient visits, admissions, and emergency department (ED) visits.

Admission diagnosis and department will be included as descriptive variables - partly to ascertain whether there are patterns in where the screening has the greatest impact, and partly to assess whether there is selection bias in the study.

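### The only CAT described is taken during a hospital stay but is read as everyday symptom burden, so the wording should be limited and the score shown by admission diagnosis

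*Protocol article*

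**What the plan says.** Four parts of the protocol article settle when the CAT is taken.

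- Study setting: "Study participants are identified during hospitalization at the participating hospitals, that is admission to emergency, medical and surgery departments".
- Data collection, Baseline: "Baseline data are derived from lung function measurements and the interviews and questionnaires completed at inclusion".
- Data collection, Five-year follow-up: later information is obtained "through linkage to national Danish registers". No repeat questionnaire is described.
- Self-reported demographic variables: the CAT is introduced as a validated questionnaire meant to "assess various aspects of their daily respiratory symptoms and limitations in daily activities".

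The Discussion then states what the score will show. It "will provide valuable insights into the daily symptom burden experienced by both smokers and non-smokers within this patient group", and: "These unique data will offer an in-depth understanding of the respiratory-related everyday experiences of socially marginalized people in Denmark". The next sentence considers a finding of higher symptom burden, morbidity and mortality linked to smoking, and says this might justify further study of cessation treatment or harm reduction.

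On the reason for admission, Clinical variables says: "Admission diagnosis and department will be included as descriptive variables". The stated purposes are to look for patterns in where screening has most impact and to assess selection bias. The CAT is not mentioned there.

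**The concern.** A person in hospital may report more breathlessness, cough or limitation than usual because of the illness that brought them in. If so, a score collected then describes the admission as well as ordinary life. The Discussion claims only the latter and does not qualify it. The article does recognise severe acute illness as a limitation, but only for spirometry and the prevalence estimate.

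Two conclusions are exposed. The first is the level: the CAT could overstate the everyday respiratory burden of this population. The second is the smoking comparison that the Discussion has in view. If respiratory admissions are more frequent among smokers than non-smokers, or the reverse, part of any difference in CAT would reflect the mix of admission reasons.

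**Working it through.** **Timing set against interpretation**

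1. Recruitment takes place during hospitalization (Study setting).
2. Questionnaires are completed at inclusion (Baseline), hence during that stay.
3. Follow-up is by register linkage (Five-year follow-up), and registers hold no CAT. The inclusion CAT is therefore the only one described.
4. The Discussion reads it as daily burden and everyday experience.
5. Nothing in the article ties the answers to the state before admission, repeats the CAT after discharge, or relates it to the reason for admission.

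Steps 1 to 3 fix the timing and step 4 fixes the reading. The article does not bridge the two.

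**Possible size**

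There is no CAT figure to reproduce: the article gives no CAT mean, standard deviation, target difference or planned test. The sample size of 511 belongs to the prevalence comparison and does not enter here. All inputs below are assumptions.

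- d = points that the admission illness adds to the CAT in an affected patient: 2, 5 or 8.
- q_S, q_N = share of smokers and of non-smokers affected.
- Inflation of a group mean = q × d.
- Shift in the smoker minus non-smoker difference = (q_S − q_N) × d.

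| q_S vs q_N | Result | d = 2 | d = 5 | d = 8 |
|---|---|---|---|---|
| 30% vs 30% | mean in smokers | 0.6 | 1.5 | 2.4 |
| | difference | 0 | 0 | 0 |
| 30% vs 20% | mean in smokers | 0.6 | 1.5 | 2.4 |
| | difference | 0.2 | 0.5 | 0.8 |
| 40% vs 20% | mean in smokers | 0.8 | 2.0 | 3.2 |
| | difference | 0.4 | 1.0 | 1.6 |
| 40% vs 10% | mean in smokers | 0.8 | 2.0 | 3.2 |
| | difference | 0.6 | 1.5 | 2.4 |

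Example: 0.40 × 8 = 3.2 points on the mean, and (0.40 − 0.10) × 8 = 2.4 points on the difference.

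The level is inflated whenever d and q are above zero, even with equal shares. The difference shifts only when the shares are unequal, and it changes sign if non-smokers are the more affected group. If patients in fact answer for their usual state, d is near zero and both effects vanish.

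**The case against.** The strongest reply is that no analysis has been fixed badly. The CAT is not among the baseline or five-year outcome measures, and Statistical considerations plans no CAT comparison. The two smoking groups appear together only in Discussion prose, and how a secondary questionnaire is tabulated is normally left to the analysis plan. This stands, and it makes the point minor. It does not remove it, because the everyday reading is asserted in the article itself.

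A reader might infer several stronger claims that the document does not support.

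- *That acute illness is demonstrably mixed into the score.* The article names emergency, medical and surgery departments, and planned admissions are not excluded. Inclusion requires ability to comply with study procedures, which would tend to keep out the most severely ill. Interview details are in a supplement that is not shown and may set a reference period. Only a possible effect can be claimed.
- *That the smoking comparison is biased.* This needs unequal shares of respiratory admissions, which nothing in the article shows.
- *That the CAT result is used to argue for more intensive cessation treatment.* The sentence is conditional, combines symptom burden with morbidity and mortality, and goes no further than possible further investigation.
- *That using admission diagnosis descriptively is a defect.* It is not. Tabulating the CAT by admission diagnosis is itself a descriptive use and fits the present text.
- *That a smoking difference driven by respiratory admissions would be wholly spurious, so that the non-respiratory stratum gives the right answer.* Respiratory admission may lie on the path from smoking through chronic lung disease to symptoms. Restricting to the other stratum, or adjusting for admission diagnosis, could understate a real association.

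**Conclusion.** The point holds as one of interpretation. A single CAT collected during a hospital stay is described without qualification as daily burden and everyday experience. Symptoms from the admission illness may raise the score, and may distort a smoking comparison if respiratory admissions differ by smoking status.

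The size cannot be derived from the document. The illustrative ranges of 0.6 to 3.2 points for a group mean and 0 to 2.4 points for the smoking difference rest entirely on assumed values for the added points and the affected shares.

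Importance is minor, since the listed outcomes, the sample size and the planned models are untouched. The point is also separate from who receives the CAT. The variables section refers to patients diagnosed with COPD and the Discussion to a wider group, but settling that would leave the timing question as it is.

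**What to change.** 1. In the Discussion, describe the CAT result as respiratory symptom burden reported during hospitalization, in place of daily burden and everyday experience. If the questionnaire sets a reference period, state it.
2. Present CAT, overall and by smoking status, for all patients and then separately for respiratory and non-respiratory admission diagnoses, using the admission diagnosis already collected.
3. Show the two strata side by side. Do not rest statements about smoking on the non-respiratory stratum alone, and say why: respiratory admission may itself result from smoking.

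The cost is one descriptive table and a few reworded sentences, with no new data collection. The drawbacks are smaller numbers in each stratum and a more limited conclusion about everyday life.

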## Data Availability

No datasets were generated or analysed during the current study.
